##### Mediation effect

To explore the possible underlying mechanisms of PA change, potential mediators of the PA behaviour intervention effect will be explored. Based on the I-Change model (Fig. 2), a multiple mediation analysis with condition (intervention vs. control condition) as the independent variable; intention and self-efficacy as mediator variables and PA behaviour as the dependent variable will be conducted. Preacher and Hayes’s SPSS macro for multiple mediator models will be used for testing the mediation hypothesis [44].

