**Fig. 1 Fig1:**
[figure not shown]
Screenshot of the PURE-eHealth-Physical Activity website

The theoretical background underlying the intervention was based on the I-Change Model [8] (Fig. 2) which incorporates several socio-cognitive models, including the theory of planned behaviour [35], the Transtheoretical Model [36], the Precaution Adoption Process Model [37] and the goal-setting theory [38]. This model has been used successfully to develop computer-tailored interventions targeting various health-related behaviours. The model assumes the following three phases in the behavioural change process: (1) raising awareness about the need to change a given health behaviour; (2) motivation to change behaviour and (3) specifying actions required to translate intention into the final goal behaviour. Raising awareness assumes the existence of sufficient knowledge, the perception of high risk and the existence of internal and external cues to action. Motivation can be increased by emphasizing the advantages of the desired behaviour and tackling perceived disadvantages. An individual’s motivation can also be enhanced by increasing the perceived social support, modelling and social norms in favour of the desired behaviour and by increasing self-efficacy to perform the intended behaviour. These factors constitute a person’s level of intention towards the desired behaviour. Translation of intention into actual behaviour is dependent on a person’s skills and action planning.

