#### Evaluation

Participants have to complete the following two questionnaires on the study website: 1) the baseline questionnaire (T0) and 2) the follow-up questionnaire 3 months after baseline (T1). The baseline questionnaire will assess the following demographics: gender, age, marital status, education, occupation, ethnicity, weight and height. Participants’ PA level will be assessed using a validated questionnaire [39]. The psychosocial determinants of the I-Change Model related to PA (intention, attitude, social influences, self-efficacy) will be assessed on a 7-point Likert scale [27]. The 3-month follow-up questionnaire consists of PA level reassessment as well as two I-Change Model variables, intention and self-efficacy. In addition, the follow-up questionnaire also consists of process evaluation questions in order to evaluate participants’ opinion of the intervention.

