##### Efficacy of the intervention

The efficacy of the PA intervention, 3 months after baseline, will be assessed with linear mixed models. This statistical analysis is very well suited for modelling data containing repeated measures from several participants [41] and has the advantage of providing better capabilities to handle missing observations compared to more traditional approaches, such as repeated measures ANOVA [42, 43]. It is essentially a general linear model, with the addition of random effects to account for the two sources of variability, within (e.g. time 0, time 1)- and between (e.g. intervention, waiting list control group)-subject variance [41]. Analysis will be adjusted for socio-demographic characteristics and PA variables that significantly differ between study arms at baseline.

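### The mediation section fixes neither time points nor use of T0 values; fitted as written on T1 data, it biases the indirect effect upward if the intervention moves intention or self-efficacy

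*Protocol article*

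**What the plan says.** Under Objectives and design, the protocol article makes mediation by motivational factors the second specific question of its first objective. The Mediation effect section gives the purpose: "To explore the possible underlying mechanisms of PA change, potential mediators of the PA behaviour intervention effect will be explored". It then specifies "a multiple mediation analysis with condition (intervention vs. control condition) as the independent variable", with "intention and self-efficacy as mediator variables and PA behaviour as the dependent variable will be conducted", to be fitted with an SPSS macro for multiple mediators. It gives no time point for mediators or outcome, no baseline covariate and no change score.

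The Evaluation section has two questionnaires, at baseline (T0) and at 3 months (T1). Intention, self-efficacy and PA are all collected at T0. Of T1 it says: "The 3-month follow-up questionnaire consists of PA level reassessment as well as two I-Change Model variables, intention and self-efficacy".

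The only rule on baseline adjustment is in the section Efficacy of the intervention: "Analysis will be adjusted for socio-demographic characteristics and PA variables that significantly differ between study arms at baseline". It is not repeated for the mediation model, and its terms would not bring in T0 intention or T0 self-efficacy.

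**The concern.** A mediator that the intervention can act on has to be measured after randomisation. Session four also assesses self-efficacy, but only among people using the intervention, so it cannot serve a two-arm model. That leaves T1, where mediators and PA are answered in one questionnaire.

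The path from condition to mediator is protected by randomisation. The path from mediator to PA is not, and two things can distort it:

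- **Stable differences between people.** Someone who is generally motivated and active will report both higher intention and self-efficacy and more PA at T1, whatever the arm.
- **Reverse causation.** From session five onward, participants see their PA compared with baseline, and those who improved are complimented. Achieved PA can therefore raise self-efficacy and intention by T1.

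At stake is the answer to a stated study question. The Conclusion says the results should inform a full-scale trial, and an inflated indirect effect could misdirect which determinants a later version targets.

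**Working it through.** **1. The plan's own figure.** The mediation analysis has none. The sample size reproduces as a within-between interaction with f = .10, r = 0.5, m = 2 measurements and alpha 0.05: λ = f²·N·m/(1 − r) = 0.01 × 200 × 2 / 0.5 = 8, with 1 and 198 degrees of freedom. Power is 0.804 and the smallest N is 200, as stated. This does not bear on the bias. It only shows what effect the plan is powered for: with change variance 2(1 − r) = 1 and 100 per arm, the arm difference in mean change has variance 1/100 + 1/100 = 0.02, and 0.40²/0.02 = 8, so f = .10 is a difference in change of about 0.40 SD.

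**2. Size of the bias, one mediator.** These assumptions are not in the documents:

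- mediator and PA have unit variance within arm;
- one stable trait supplies a share s of the variance of each at both waves, with no other link between them;
- the arm effect on the mediator is 0.30 SD;
- the true mediator effect on PA is zero.

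Under this model the T0–T1 correlation of PA is also s, so s = 0.5 matches the r = 0.5 in the Sample size section.

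- T1 on T1, no T0 term: path b = s, so the indirect effect is 0.30·s.
- T0 mediator and T0 PA as covariates: b = s/(1 + 2s), so the indirect effect is 0.30·s/(1 + 2s).
- Change scores: the trait cancels, so b = 0.

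| s | No T0 term | T0 covariates | Change scores |
|---|---|---|---|
| 0.3 | 0.30 × 0.3 = 0.090 | 0.090/1.6 = 0.056 | 0 |
| 0.4 | 0.30 × 0.4 = 0.120 | 0.120/1.8 = 0.067 | 0 |
| 0.5 | 0.30 × 0.5 = 0.150 | 0.150/2.0 = 0.075 | 0 |

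Simulation at N = 200 (1,500 trials per scenario) gives 0.090, 0.117 and 0.148 without T0 terms, and 0.057, 0.065 and 0.075 with them. The true value is 0 throughout.

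**3. False findings, two mediators.** This used 600 simulated trials per scenario at N = 200, with a Monte Carlo 95% interval for the total indirect effect and a true mediator effect of zero. Assumed: stability 0.5 (stated for PA only), a trait correlation of 0.5 between the mediators, and a trait correlation of 0.3 to 0.5 between each mediator and PA.

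| Arm effect on mediators | No T0 term | T0 covariates | Change scores |
|---|---|---|---|
| 0 | 2–4% | 0–1% | 0–0.3% |
| 0.3 SD | 41–72% | 7–22% | about 3% |
| 0.5 SD | 70–98% | 12–29% | 4–5% |

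At 0.3 SD the mean spurious indirect effect was 0.07 to 0.12 SD without T0 terms, 0.02 to 0.045 SD with T0 covariates, and about 0 with change scores. These differ from step 2 because a trait correlation is not the same quantity as a trait share.

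**4. What the check does not cover.** Both steps model stable differences only. A temporary state that affects both sets of answers at T1, or PA acting back on the mediators, is not carried by the T0 values, so neither covariates nor change scores remove it.

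**The case against.** **The section is silent; it does not exclude T0 values.** A reader might infer that the plan rules them out. The documents do not support that. The stated aim concerns PA change, T0 values of all three variables exist, and an article may leave covariates to the full plan. This stands, so the bias is conditional on fitting the model as written. The measurement schedule, however, is fixed: whatever an analysis plan adds, mediators and outcome remain concurrent.

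**Randomisation protects part of the product.** A reader might infer that stable differences alone create mediation, or that any shift in the mediators guarantees a positive answer. Neither follows. With no arm effect on the mediators, false findings were 2–4%; at 0.3 SD they were 41–72%, not certain.

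**The size can be overstated.** The spurious 0.09–0.15 SD is close to the pooled effect of 0.16 cited in the Background, which might suggest that it equals the whole expected effect. That figure is not the plan's target. Against about 0.40 SD it is 0.09/0.40 = 23% to 0.15/0.40 = 38%.

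**T0 covariates are an incomplete remedy.** This stands. In step 2 they leave 1/(1 + 2s), or 50% to 63%, of the bias. Hence the change-score analysis and the limit on the conclusion.

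**Mediator order.** The account of the I-Change Model says that self-efficacy, among other factors, makes up a person's "level of intention towards the desired behaviour", so a reader might want a serial model. The documents do not require one: the study question asks for no serial decomposition, and the section does not say how the two mediators are ordered. In linear models with the same variables, the total indirect effect is identical either way. A serial model would also add another concurrent, non-randomised path.

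**Exploratory status.** This stands and limits the consequence, although mediation remains a stated question.

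**Conclusion.** The point holds in conditional form. The Mediation effect section fixes neither time points nor use of T0 values, and the design makes the mediator-PA path concurrent and non-randomised. If the model is fitted as written on T1 values and the intervention moves intention or self-efficacy, stable differences between people bias the indirect effect upward. The sizes rest on the assumed trait shares of 0.3–0.5, the assumed 0.30 SD arm effect and a true mediator effect of zero: about 0.09–0.15 SD with no T0 term, about 0.06–0.075 SD with T0 covariates, and about 0 with change scores under the same trait model. The result depends strongly on the arm effect on the mediators; without one, false findings stay at or below 5%. The efficacy test is not affected.

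**What to change.** In the Mediation effect section:

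1. State that T1 intention and T1 self-efficacy are the mediators and T1 PA is the outcome.
2. Enter T0 intention, T0 self-efficacy and T0 PA as covariates in every path, whether or not they differ between arms at baseline.
3. Add a change-score version as a sensitivity analysis.
4. Limit the conclusion to 'consistent with mediation', and say that mediators and outcome were measured together, so that same-wave confounding and reverse causation remain possible.

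The cost is a few sentences and one extra model. All the variables are already collected at both waves, and nothing changes in the sample size, the schedule or the efficacy analysis.

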##### Use of the intervention

Logistic regression will be conducted with *intervention initiation* (first Website visit, 0 = no/1 = yes) as the dependent variable and demographics status will be included in the model as predictors of intervention initiation. The same independent variables will be considered in the model, with the addition of the intention to be physically active, as predictors of *intervention completion*.

### Ethics study approval

The study protocol was approved by the ethics committees of the Université du Québec à Trois-Rivières (CER-13-192-06.32) and the Institut Universitaire de Cardiologie et de Pneumologie de Québec (21002).

### Baseline characteristics

Among the 2790 Quebec City PURE participants, 1269 were eligible to participate in the present study, of which 244 actually signed up. The socio-demographic and clinical characteristics of these 244 participants are described in Table 1. Participants had a mean age of 56 years, were mostly women (67.6 %) and have completed their college/university degree (83.6 %). Half of the population were overweight or obese, 12 % had hypertension and 2 % diabetes.

**Table 1 Tab1:** Characteristics of the randomized participants

Number of participants, *n*	244		
Mean age (*SD*), [range], years	56.3	(7.0)	[39–70]
Gender, *n* (%)			
female	165	(67.6)	-
male	79	(32.4)	-
Highest education level completed, *n* (%)			
high school	40	(16.4)	-
college/university	204	(83.6)	-
Smoking behaviour, *n* (%)			
current	14	(5.7)	-
never	127	(52.0)	-
former	103	(42.2)	-
Body mass index, *n* (%), kg/m^2^			
underweight (16.5-17.99)	2	(0.8)	-
normal (18–25)	112	(45.9)	-
overweight (25.01–29.99)	90	(36.9)	-
obese (30+)	40	(16.4)	-
Mean blood pressure (*SD*), [range], mm Hg			
systolic	127.0	(18.3)	[85–189]
diastolic	80.0	(11.0)	[55–117]
Mean low-density lipoprotein level (*SD*), [range], mmol/L	3.01	(0.8)	[1.21–5.57]
Mean high-density lipoprotein level (*SD*), [range], mmol/L	1.66	(0.44)	[.83–3.20]
Mean apolipoprotein B level (*SD*), [range], mmol/L	0.91	(0.24)	[.32–1.65]
Mean glycemia level (*SD*), [range], mmol/L	5.0	(0.7)	[3.7–10.2]
Participants reported risk factors, *n* (%)			
Hypertension	29	(11.9)	-
Diabetes	5	(2.0)	-
Medications, *n* (%)			
Anti-hypertensive medication	26	(10.7)	-
Hypoglycemic medication	2	(0.8)	-

## Discussion

The main objective of this paper was to describe the rationale, design, development of the content and baseline characteristics of participants enrolled in a randomized controlled trial of a web-based computer-tailored PA intervention. We hypothesize that at the 3-month follow-up, participants in the intervention condition will show higher levels of moderate- to vigorous-intensity PA compared to the control group. In line with current priorities, we focus intervention development on two groups: women and individuals with a low-to-moderate education level. The overall participation rate was 19 %, which is comparable to other web-based, computer-tailored, PA interventions (15 % [19], 15 % [45], 29 % [46]). Women constitute two-third of the 244 participants. However, only 15 % of the participants had a low-to-moderate education levels. These participation rates are not unique to our study; other web-based PA interventions also reported that participants were mostly women [28, 45, 47–49] and highly educated [19, 28, 45, 47–51].

In the context of the Quebec healthcare system and in compliance with the recommendations of the Health and Welfare Commissioner [52], the integration of the proposed technology presents a new means of offering services that include programs to promote heart health and prevent cardiovascular disease. In the Quebec healthcare system [53], as well as elsewhere [54], lack of time is often a major impeding factor for health care professionals when it comes to face-to-face counselling. Computer-tailoring technology is one of the most significant innovations developed over the last decade in the field of support services for face-to-face counselling. People are likely to benefit from access to a web-based self-management platform that can be tailored and adapted to each individual in the comfort of their own home without being restricted to the limited time of busy health care professionals. Despite the sustained growth of this type of technology in the scientific community over the past 20 years, its use is still in the early stages in the province of Quebec. The results of this study will contribute to the development of data that will provide answers to some emerging research questions in the field of computer-tailoring, such as reaching high-risk groups [55] and establishing larger effect sizes [15].

This study has several strengths. First, the use of video-driven messages in the context of web-based computer-tailored interventions is promising and innovative. In terms of methodology, the use of a randomized controlled trial is a strength because it decreases possible bias (internal validity). Finally, by reaching participants directly in their homes (no clinical office visits), the proposed web-based intervention could have a major public health impact. The study also has limitations. The outcome measure is based on self-reporting using the Godin Leisure-Time Exercise Questionnaire. Nevertheless, it has been demonstrated that the reliability and validity of this tool compared favourably to nine other self-report measurements [56]. The Pure-eHealth-Physical Activity intervention is only available on the Internet and thus excludes participants who do not have access to the Internet, which is more likely to be the case among people with a low level of education. However, the 2009 Canadian Internet Use Survey pointed out that the gap is narrowing in terms of Internet users between the lowest (76 %) and highest (92 %) quartiles of income [57]. In addition, while the participants may know how to use the Internet, they may not be familiar or willing to comply with this new intervention. Studies such as this one are crucial to assess the participation rate and the impact of these interventions.

## Conclusion

This paper provides insight into the development of a web-based computer-tailored PA intervention for Canadian adults aged 35 to 70 years of age. The results of this study will have useful information about the feasibility, effects, appreciation and use of this intervention. This insight needs to be considered before embarking on a full-scale RCT to assess the long-term benefit and cost-effectiveness of the intervention on PA.
